## Methods and analysis

### Study design

This is an NI trial designed to assess the impact of UNIMMAP MMS and Ca (500 mg) taken concurrently, relative to taking them separately, on haematological and iron status of women and infants. Women will be individually randomised in a 1:1 ratio to take both supplements in the morning (‘together’) or to take the MMS in the morning and the calcium in the evening (‘separate’). Counselling messages and supplement packaging will not enable blinding of participants or study staff with direct participant contact. However, laboratory staff measuring the trial’s outcomes and investigators not directly involved in field work will be blinded. The code will be broken when all outcomes have been assessed. Enrolment commenced in Pakistan on 25 August 2025 and in Burkina Faso on 12 September 2025. Assuming an 8-month recruitment period for Burkina Faso and a 12-month period for Pakistan, we anticipate that field work will be completed by May 2027.

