Exploratory outcomes, defined as pre-specified outcomes not included in the confirmatory analysis and for which the trial was not powered to detect differences, include anaemia (Hb<110 g/L) at 30<34 weeks and, as an indicator of intervention safety, severe anaemia (Hb<70 g/L) at 20<24 weeks and 30<34 weeks of gestation. Other exploratory outcomes, defined in table 2, include iron deficiency, iron deficient erythropoiesis, iron deficiency anaemia, birth weight, LBW, gestational age at birth, weight-for-gestational age (GA) Z-score, small-for-gestational age, miscarriage and stillbirth.

**Table 2 T2:** Definitions of exploratory outcomes to be assessed in the CaMMS trial

Exploratory outcomes	Definition
Anaemia	Hb<110 g/L at 30<34 weeks of gestation
Intervention safety	Severe anaemia (Hb<70 g/L) at 20<24 weeks or 30<34 weeks
Iron deficiency	Plasma ferritin<15 µg/L at 30<34 weeks of gestation^*^
Iron-deficient erythropoiesis	sTfR concentration>8.3 mg/L at 30<34 weeks of gestation
Iron deficiency anaemia	Concurrent anaemia (Hb<110 g/L) and iron deficiency (plasma ferritin<15 µg/L)^1^ at 30<34 weeks of gestation
Birth weight	Infant weight within 72 hours of birth
Low birth weight	Infant weight<2500 g within 72 hours of birth
Gestational age (GA) at birth	GA at birth in weeks based on screening ultrasound and INTERGROWTH-21st standard
Preterm birth	GA at birth<37 weeks of gestation
Weight-for-gestational age Z-score	Calculated based on weight≤72 hour of birth using the INTERGROWTH-21st standard
Small-for-gestational age	<10th percentile of weight-for-gestational age using INTERGROWTH-21st standard
Miscarriage	Foetal loss <20 gestational weeks
Stillbirth	Foetal loss ≥20 gestational weeks

* An alternative physiologically based ferritin threshold of 25 µg/L will be used in sensitivity analyses based on recent evidence that this higher threshold may better identify individuals at an earlier stage of iron deficiency, when iron stores are insufficient for red blood cell production and other tissue functions.

CaMMS, calcium and multiple micronutrient supplement; Hb, haemoglobin ; sTfR, soluble transferrin receptor.

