### Sample size

For this NI trial, we calculated an NI margin using guidelines developed by the US Food and Drug Administration and the European Medicines Agency.^35^ Briefly, the NI margin is based on effect sizes from prior meta-analyses or trials of the active control, with the smallest expected treatment effect (M1) set at the limit of the 95% CI that is closest to the null effect. We found no studies comparing the effects of MMS and calcium taken together versus placebo, and data comparing MMS to a placebo were similarly limited. We therefore used the pooled effect size for Hb concentration at or near term (8.88 g/L (95% CI 6.96 to 10.8)) from 20 trials of iron-containing supplements, compared with the same formulations without iron, no treatment or a placebo.^36^ As the lower limit is clinically large (7.0 g/L), common practice is to preserve 50% of the minimum effect for an NI margin (M2) of −3.5 g/L. However, the absolute value of this effect exceeds 3.0 g/L, which we would consider clinically meaningful based on the difference between the third and fifth normative centiles for maternal Hb at 30<34 weeks’ gestation derived from the INTERGROWTH-21st Project,^37^ that is, the difference between a probable diagnosis of being at high risk versus anaemic. Therefore, we selected a more conservative NI margin of −3.0 g/L.

We assumed a one-sided α=0.025; 90% power; an SD of 17 g/L, based on prior data from both sites and assuming equal group variance across treatment arms^38,39^; and 15% loss to follow-up. Accordingly, a sample of 1600 women per country (3200 women in total) will be required to conclude NI, in each country independently; that is, that the lower limit of the 95% CI around the difference in Hb concentration between the intervention (MMS and Ca taken together) versus control (MMS and Ca taken separately) is greater than −3 g/L.

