#### ANC follow-up visits

After enrolment, women will be seen by research staff every 4 weeks and encouraged to attend all recommended ANC visits. In Burkina Faso, these visits will coincide with routine antenatal care. In Pakistan, except for the 20<24 and 30<34 week visits, follow-ups will take place at the home. At each visit, adherence will be assessed by asking about supplement use on the prior day, including: whether the woman took each of the supplements, whether they were taken together or separately, at what time each of the supplements was taken, and whether each of the supplements was taken with or without food. Women will also be asked how many days in the past week they took each of the supplements. Finally, we will count and record the number of tablets remaining in the blister packs. Additional supplements will be dispensed so that women always have an 8-week supply. Staff will also collect morbidity information and abstract health card data on anthelminthic medication, sulfadoxine-pyrimethamine (Burkina Faso only), and low-dose aspirin. Providers at both sites will be trained to clearly record any blood transfusions, IV iron, and iron-containing supplements for data abstraction, and women will be asked to keep prescriptions and medication boxes. Information on all locally available iron-containing supplements, including photographs of packaging, was collected to facilitate data capture.

For visits in the windows of 20<24 and 30<34 weeks, women will also undergo a physical exam (including anthropometric measurements and blood pressure) and dietary intake assessment. The exam will include the venous blood draw, as described above. On-site Hb testing will be done using the HemoCue device for the purpose of identifying women with Hb<70 g/L and referring them for care while they are at the clinic. The primary trial outcome and safety outcome will be based on results of the CBC. These results will be reviewed after each visit to identify any cases of severe anaemia that were missed by on-site HemoCue testing. These women will be contacted and referred for care; their outcome data will be retained in the analysis. In Burkina Faso, malaria rapid diagnostic testing will also be done and, if positive, women will be referred for treatment.

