### Statistical methods

The statistical analysis will be structured around three pre-specified estimands, defined in accordance with the ICH E9(R1) Addendum and described in online supplemental table 1. Anticipated intercurrent events and their handling strategies are specified in online supplemental table 2. Briefly, the primary estimand applies a treatment policy strategy across all randomised women (ITT); the secondary estimand applies a per protocol strategy restricted to adherent women; and the sensitivity estimand applies an analysis restricted to women who did not develop severe anaemia prior to outcome ascertainment (mITT). The analyses described below correspond to these three estimands.

For analysis of the primary outcome—Hb measured by haematology analyser at 30<34 weeks of gestation—we will apply all three estimands. For the per protocol analysis, we will use a two-tier approach to characterise adherence. The first tier will quantify the median pill count per monthly follow-up visit. The second tier will quantify the percentage of monthly follow-up visits and household visits where women self-reported taking calcium and MMS at the appropriate time on the previous day, that is, the time prescribed for their assigned study arm. The per protocol dataset will include subjects who consumed a median of ≥75% study supplements per month based on pill count and consumed supplements at the prescribed time on the prior day at ≥75% of visits. The mITT dataset will include subjects who were not diagnosed with severe anaemia (Hb 70 g/L) during follow-up period.

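### The mITT sensitivity set is defined two ways, and the dataset wording removes women on the primary outcome value itself, which pulls the estimate toward non-inferiority if the together arm is worse

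*Protocol article*

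**What the plan says.** All references are to the protocol article.

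- Statistical methods, first paragraph, describes the sensitivity estimand as an analysis "restricted to women who did not develop severe anaemia prior to outcome ascertainment (mITT".
- The following paragraph defines the dataset: "The mITT dataset will include subjects who were not diagnosed with severe anaemia (Hb 70 g/L) during follow-up period". The missing less-than sign may be lost in text extraction and is not held against the plan.
- Outcomes, Table 2, defines the safety outcome as "Severe anaemia (Hb<70 g/L) at 20<24 weeks or 30<34 weeks". The second of those visits is the primary-outcome visit.
- ANC follow-up visits states that the primary and the safety outcome both come from the CBC. Of women whose severe anaemia was missed on site, it says that "their outcome data will be retained in the analysis".
- Statistical methods makes ITT primary, examines ITT and PP for consistency, and warns that PP may select differentially after randomisation. It gives no such warning for mITT.
- The same section applies ITT, PP and mITT to the secondary and exploratory outcomes. Severe anaemia is one of the exploratory outcomes.

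**The concern.** The two sentences select different women. Under the estimand wording, a woman leaves the set because of a low Hb before the outcome visit. Under the dataset wording, she can also leave because her 30<34-week Hb, which is the primary outcome, is below 70 g/L.

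Hb below 70 g/L is the low tail of the endpoint. If taking the supplements together lowers Hb, more women cross that line in the together arm, more of them are removed, and the remaining difference shrinks toward zero. A sensitivity analysis in a non-inferiority trial should be able to unsettle a favourable result. This rule makes a favourable result more likely exactly when the deficit is real.

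**Working it through.** **Inputs from the article.** "We assumed a one-sided α=0.025; 90% power; an SD of 17 g/L"; "we selected a more conservative NI margin of −3.0 g/L"; "15% loss to follow-up"; "Women will be individually randomised in a 1:1 ratio"; severe anaemia cut-off 70 g/L.

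**Assumptions (not in the article).** Normal Hb; control mean 110, 105 or 100 g/L; between-visit correlation 0.6; together-arm deficit of 1.5 or 3 g/L at 20<24 weeks; true deficit at 30<34 weeks set at the margin, −3 g/L; at first, no effect of treatment after referral.

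**1. The plan's own figure.** n per arm = 2(1.960 + 1.282)² × 17² / 3² = 675, taking a true difference of 0. Dividing by 0.85 gives 795 per arm, or 1590 per country against the stated 1600. With 800 × 0.85 = 680 evaluable per arm, SE = 17 × √(2/680) = 0.922 and power is 90.2%. The plan reproduces.

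**2. Truncation at the outcome visit alone, mean 100.** With a = (70 − μ)/17 and λ = φ(a)/(1 − Φ(a)), the retained mean is μ + 17λ.
- Separate: a = −1.765, λ = 0.0875, retained mean 101.49, 3.9% removed.
- Together (μ = 97): a = −1.588, λ = 0.1197, retained mean 99.04, 5.6% removed.
- Difference: −2.45 g/L instead of −3.00.

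**3. All readings.** Rows that involve the 20<24-week visit come from simulation of two correlated visits, with Monte Carlo error of about 0.01–0.02 g/L. The percentage is the chance that the lower 95% limit clears −3, Φ((difference + 3)/0.922 − 1.96). It is 2.5% when every woman is kept.

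| Women removed if Hb below 70 at | Mean 110 | Mean 105 | Mean 100 |
|---|---|---|---|
| 30<34 weeks only | −2.79 (4.2%) | −2.64 (5.8%) | −2.45 (8.6%) |
| Either visit (dataset wording), mid-pregnancy deficit 1.5 | −2.76 (4.4%) | −2.62 (6.1%) | −2.43 (9.0%) |
| Either visit (dataset wording), mid-pregnancy deficit 3 | −2.71 (4.9%) | −2.54 (7.3%) | −2.32 (11.0%) |
| 20<24 weeks only (estimand wording), mid-pregnancy deficit 1.5 | −2.94 (2.9%) | −2.90 (3.2%) | −2.84 (3.7%) |
| 20<24 weeks only (estimand wording), mid-pregnancy deficit 3 | −2.87 (3.4%) | −2.78 (4.2%) | −2.67 (5.5%) |

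Truncation also shrinks the SD. Using the SE of the retained women instead of 0.922 raises the percentages slightly, to about 12% at most.

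**4. Treatment after referral.** Suppose women below 70 g/L at 20<24 weeks gain an assumed amount by the outcome visit (mean 100, mid-pregnancy deficit 3). Under the estimand wording:
- gain of 20 g/L: ITT −2.66, mITT −2.67;
- gain of 35 g/L: ITT −2.40, mITT −2.68.

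So mITT is the more favourable with little or no gain, about equal at 20 g/L, and the less favourable with a large gain. Under the dataset wording mITT stays at about −2.3 whatever the gain, because these women are already out, and it was nearer to zero than ITT in every case run.

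**5. No true difference.** The same share leaves each arm and the expected estimate stays at 0.

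**6. Severe anaemia as an outcome.** Under the dataset wording every woman with the event is outside the set, so both arms have zero events.

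**The case against.** Several counter-arguments stand.

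- The larger figures belong to the dataset wording. The article says that its analyses correspond to the estimands, and on the estimand wording the selection is on an earlier, correlated Hb, with a smaller shift.
- Eligibility trims the low tail, because women with baseline Hb below 70 g/L are not enrolled or are excluded. Modelling this at mean 100, with a baseline mean assumed 3 g/L higher, lowers removals at either visit from 9.4% against 6.6% (together against separate) to about 8.1% against 5.5%, and the error from about 11% to 10%.
- The supplemental tables on estimands and intercurrent events, and the SAP, are not shown and may settle the window. The article also plans to examine effect modification by receipt of iron treatment.

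A reader might infer three stronger things that the documents do not support.

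- That the trial's type I error is inflated: it is not, because ITT is primary and the decision rule names ITT and PP, not mITT.
- That mITT will always confirm non-inferiority, or always errs the same way as ITT: under the estimand wording this depends on a treatment effect that the article does not give.
- That retaining severely anaemic women's data contradicts mITT: that sentence fits the ITT analysis.

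What the objections do not remove is that two windows are printed, and that one of them cuts the primary outcome at 70 g/L.

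**Conclusion.** The point holds for the mITT analysis, not for the trial's main decision. As printed, the article does not fix which women form the set. Followed literally, the dataset wording biases the mITT estimate toward non-inferiority whenever the together arm is truly worse. At a true deficit of 3 g/L the shift is about 0.2 to 0.7 g/L, and the chance of clearing the margin is about 4% to 11% instead of 2.5%, for assumed control means of 110 down to 100 g/L.

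The estimand wording still selects after randomisation. Its shift is about 0.05 to 0.35 g/L, and whether it lies nearer to non-inferiority than ITT depends on treatment after referral. The direction of the dataset-wording bias held in every scenario with a true deficit. Its size rests on the assumed means, correlation and mid-pregnancy deficit.

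**What to change.** - Delete the dataset wording and use one window throughout, so that no woman is excluded because of her 30<34-week Hb.
- Do not apply mITT to severe anaemia.
- State that mITT is selected after randomisation and will not be read as corroborating non-inferiority.
- Preferably, replace the exclusion with a sensitivity analysis that keeps every randomised woman and treats transfusion, IV iron or extra iron before the outcome as the intercurrent event, for example by imputing the untreated 30<34-week Hb from CBC values before that treatment. Simply carrying a 20<24-week value forward is weaker, because it ignores change with gestation.

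The cost is wording in the protocol and SAP; the sample size does not change. The preferred replacement relies on model-based values for a small number of women, and its assumptions would have to be stated in advance.

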### Study setting

In Burkina Faso, the study will be conducted in Sandbongtenga Province, approximately 100 km northeast of Ouagadougou. The province’s altitude ranges from 350 to 400 m, while rainfall varies between 600 and 750 mm per year. The area is in a highly endemic malaria transmission zone.^27^ Malaria accounts for 57% of hospitalisations and 36% of deaths in health facilities in Burkina Faso. Four out of five cases are due to *Plasmodium falciparum*. Malaria is highly prevalent during the rainy season. Women will be recruited from three antenatal care clinics in Kaya district and two rural medical centres in the neighbouring Boussouma district.

In Pakistan, pregnant women will be recruited from the rural district of Thatta, located 103 km southeast of Karachi in Sindh Province. The district lies within the lower Indus River basin and is predominantly a low-altitude coastal plain, with elevations generally close to sea level. Malaria transmission in Thatta is endemic and follows the seasonal pattern observed across Sindh Province. Notably, Thatta has the highest annual incidence of suspected malaria in Sindh, estimated at approximately 191 cases per 1000 population.^28^ Transmission is characterised by two seasonal peaks: a smaller peak in March, coinciding with the onset of pre-monsoon rains, and a larger peak during the post-monsoon period from August to October, when increased rainfall and standing water provide favourable breeding conditions for Anopheles mosquitoes, the vectors of malaria. Both *Plasmodium vivax* and *P. falciparum* circulate in the area, with *P. vivax* accounting for most reported malaria cases. Trial activities will be carried out in one civil hospital in the district.

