### Assignment of interventions

The randomisation schema will be prepared by [name] and [name] using random permuted blocks with variable block size (4, 8 or 12) with a 1:1 allocation to the ‘together’ or ‘separate’ regimen, stratified by site and recruitment clinic. The list will include the sequence, country, health centre, randomly allocated intervention and unique participant identifier. An access-restricted, web-based, centralised allocation system covering both sites will be developed. Once a woman has provided consent for trial enrolment, the research staff will enter his or her valid username and password, the woman’s screening identification number and the enrolment date. They will then press the ‘Request New Allocation’ button and the system will reveal the next allocation to Separate or Together in the randomisation sequence, displaying the woman’s assigned 6-digit alphanumeric identification number.

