After administering the questionnaire, women will undergo a physical exam, where staff will measure women’s weight to the nearest 100 g using an ADE M316600 electronic floor scale (ADE Germany GmbH, Hamburg, Germany), height to the nearest 1 mm using an ADE MZ10042 mobile stadiometer (ADE Germany GmbH, Hamburg, Germany), mid-upper arm circumference to the nearest 1 mm, and blood pressure using the Microlife Cradle VSA (Microlife, Widnaw, Switzerland). They will then use antecubital venipuncture to collect a venous blood sample into (a) an untreated or serum-separator blood collection tube for serum-based analyses (ferritin; soluble transferrin receptor; hepcidin; erythropoietin; C-reactive protein (CRP); α_1_-acid glycoprotein (AGP)) and (b) an EDTA-treated evacuated blood collection tube for assays requiring whole blood (CBC; haemoglobinopathies; malaria parasitaemia in Pakistan). While the Hb measured by HemoCue at screening will serve as an initial screening for severe anaemia, results of the CBC will be used for the baseline Hb measurement. CBC results will be reviewed to identify any women with Hb<70 g/L who were not flagged by on-site HemoCue testing. For the baseline visit, these women will be contacted to provide a referral and will be treated as post-randomisation exclusions. Blood samples will be stored in insulated containers with cold packs prior to transit to local laboratories for processing. Finally, women will be given two boxes of study supplements (one 4-week supply and a 4-week buffer) and receive counselling, as described above.

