As treatment effects may vary between countries due to differences in the determinants of Hb concentration, we will use a two-stage approach to combine treatment effect estimates across countries. In the first stage, we will estimate country-specific treatment effects and 95% CIs using simple linear regression models with a dummy variable for allocation. We will treat these site-specific analyses as separate hypothesis tests and will not correct for multiple testing across site-specific analysis results. In the second stage, we will pool the country-specific effects. Since between-country heterogeneity in treatment effects cannot be estimated precisely with only two countries, we will present both fixed-effect and random-effects estimates across countries. The latter will be performed using the inverse variance approach with the between-country treatment effect variance estimated by the DerSimonian and Laird method. Country-specific results will be the primary basis for the NI decision; the pooled estimates are secondary summaries to present the range of plausible pooled effects without relying on an imprecise estimate of between-country heterogeneity or assuming a common effect across countries. In addition to the unadjusted analyses, we will conduct sensitivity analyses including the following baseline covariates: parity, body mass index, height and baseline values for Hb, ferritin, CRP and AGP. We will follow the same approach for the ITT, PP and mITT analyses. NI will be determined using the fixed-margin methods (figure 3). That is, if the lower limit of the 95% CI around the difference in Hb concentration between the intervention and control is greater than the NI margin of −3 g/L, the intervention will be deemed non-inferior. We will use both ITT and PP approaches. For NI trials, PP analysis provides a more conservative assessment; however, as differential adherence between arms is possible, PP analysis may introduce bias through differential post-randomisation selection based on adherence. Therefore, while both analyses will be examined for consistency, ITT will be considered primary. We will also explore effect modification based on receipt of any iron treatment, extracted from health cards, and dietary iron and calcium intakes. A *p* value<0.05 for the interaction term will be considered statistically significant.

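### The primary non-inferiority model ignores baseline haemoglobin and the clinic stratification factor, so its interval is wider than the collected data allow

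*Protocol article*

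**What the plan says.** The Statistical methods section of the protocol article estimates country-specific effects "using simple linear regression models with a dummy variable for allocation". It makes these country-specific results the main basis for the non-inferiority decision, which compares the lower 95% confidence limit with -3 g/L. The same section then adds: "we will conduct sensitivity analyses including the following baseline covariates: parity, body mass index, height and baseline values for Hb, ferritin, CRP and AGP". The same approach applies to the ITT, PP and mITT analyses.

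Under Assignment of interventions, randomisation is "stratified by site and recruitment clinic". Site is respected because the countries are analysed separately. Clinic is in neither the primary model nor the sensitivity list. Study setting gives Burkina Faso "three antenatal care clinics in Kaya district and two rural medical centres", which makes five clinics. For Pakistan it says: "Trial activities will be carried out in one civil hospital in the district".

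Under Baseline, "results of the CBC will be used for the baseline Hb measurement", so the baseline value comes from the same type of test as the outcome. The sample size rests on "one-sided α=0.025; 90% power; an SD of 17 g/L", with 15% loss and 1600 women per country.

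**The concern.** The trial succeeds or fails in each country on one confidence limit, so avoidable width directly raises the chance of failing a regimen that is truly non-inferior. The plan collects a baseline measurement of the outcome variable but leaves it out of the analysis that decides. It also stratifies allocation by clinic and then analyses as if it had not. If clinic predicts Hb, the model-based standard error is then too large, because stratification has already removed the between-clinic part of the variation from the treatment comparison.

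Gestational age at enrolment is missing from both models as well, although baseline Hb may be taken anywhere from 6 to <20 weeks.

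The loss matters most if co-administration carries a small real deficit. The 90% power figure is reproduced only with a true difference of zero, and it falls quickly below that.

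**Working it through.** **Inputs from the Sample size section:** margin 3 g/L, SD 17 g/L, one-sided alpha 0.025, power 90%, 15% loss, 1600 women per country, randomised 1:1. The true difference is not stated; zero is assumed.

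**Reproducing the plan's figure.** n per arm = 2 × 17² × (1.96 + 1.2816)² / 3² = 675. That is 1350 per country, and 1350 / 0.85 = 1589, in line with the stated 1600. Evaluable per arm: 1600 × 0.85 / 2 = 680.

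**Planned model.** SE = 17 × √(2/680) = 0.922 g/L. Half-width = 1.96 × 0.922 = 1.81 g/L. Power = Φ(3/0.922 − 1.96) = 90.2%.

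**Adding baseline Hb.** With correlation r between baseline and outcome, SE = 17 × √(1 − r²) × √(2/680), and power = Φ((3 + δ)/SE − 1.96) for true difference δ. The article does not give r, so a range is assumed.

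| Assumed r | SE (g/L) | 95% CI half-width (g/L) | Power, δ = 0 | Power, δ = -0.5 | Power, δ = -1 |
|---|---|---|---|---|---|
| 0 (planned) | 0.922 | 1.81 | 90% | 77% | 58% |
| 0.2 | 0.903 | 1.77 | 91% | 79% | 60% |
| 0.3 | 0.879 | 1.72 | 93% | 81% | 62% |
| 0.4 | 0.845 | 1.66 | 94% | 84% | 66% |
| 0.5 | 0.798 | 1.56 | 96% | 88% | 71% |
| 0.6 | 0.738 | 1.45 | 98% | 92% | 77% |

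Put another way, 90% power at δ = 0 would need 1335, 1193 or 1017 women per country at r = 0.4, 0.5 or 0.6, against 1589 without adjustment.

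**Adding clinic (Burkina Faso only).** If clinic explains a share s of the Hb variance, the unadjusted SE is too large by a factor of 1/√(1 − s). That is 1.026 at s = 5% and 1.054 at s = 10% (both shares assumed). A simulation of five equal clinics with 2000 trials per scenario agrees: SE 0.922 unadjusted against 0.898 and 0.875 with clinic in the model. Clinic plus baseline Hb (a further 25% of variance) gave SE 0.77 and 0.74 and power of about 97–98%.

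**Type I error.** At a true difference of -3 g/L, the unadjusted model's simulated error was 0.0245 (s = 5%) and 0.022 (s = 10%). Monte Carlo error is √(0.025 × 0.975 / 2000) = 0.0035, so these runs cannot distinguish either value from nominal. They show no inflation, and the SE formula puts any departure on the conservative side.

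**Is baseline Hb a legitimate covariate?** The Baseline section describes the venous sample after allocation but before supplements are handed out. The value therefore cannot reflect the study supplements.

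**The case against.** The strongest reply is that nothing here is invalid. A comparison of two means in a randomised trial is unbiased. Sample size and analysis agree with each other, since both use an unadjusted SD of 17 g/L, and the trial has its promised 90% power under its own assumptions. An analysis adjusted for baseline Hb is already prespecified and will be reported, so the dispute is over which analysis is labelled primary. All of this stands, and it limits the point to lost efficiency. It does not remove the point, because the primary label decides which confidence limit is held against -3 g/L.

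The size of the gain can also be challenged. The correlation is assumed. It could be modest, because baseline is taken at widely varying gestational ages, at least 10 weeks before the outcome, and women with Hb below 70 g/L are excluded. This also stands, so the table runs down to r = 0.2, where the gain is about one percentage point at zero difference. The direction does not change.

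The clinic term does nothing in Pakistan, which has one hospital, and helps in Burkina Faso only as far as clinic predicts Hb. That is correct. Most of the gain comes from baseline Hb. The benefit of adding gestational age is not quantified here.

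Finally, the SAP is not at hand and might add terms. But the article itself names the primary model and lists the sensitivity covariates, so this choice was not left open.

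**Conclusion.** The concern holds as a loss of efficiency. The planned analysis is valid, shows no inflation of type I error and reaches 90% power if the SD is 17 g/L, loss is 15% and the true difference is zero.

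For an assumed baseline–outcome correlation of 0.4 to 0.6, adjustment would shorten the interval by 8% to 20% and lift power to 94–98% at zero difference, or from 77% to 84–92% at -0.5 g/L. Correlations of 0.2 to 0.3 would give 91–93% at zero difference. Omitting clinic costs about 3% to 5% of the standard error in Burkina Faso if clinic explains 5% to 10% of the variance, and nothing in Pakistan.

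The change should be made because it is cheap and protects the decision where the plan is most fragile, under a small true deficit. It is not a condition of the trial's validity.

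**What to change.** Specify as the primary country-specific model a linear regression of Hb at 30<34 weeks on arm, baseline Hb from the complete blood count, gestational age at enrolment and, in Burkina Faso, indicators for recruitment clinic. Use the same model for the ITT, PP and mITT analyses and carry its estimates into the pooling stage. Report the unadjusted estimate as the sensitivity analysis, and add clinic to the longer list of sensitivity covariates. State how missing baseline values are handled, by simple or multiple imputation.

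In a linear model this leaves both the target (a difference in means) and the -3 g/L margin unchanged.

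The cost is a change to the protocol and SAP with no new data, visits or participants. Because enrolment has begun and the SAP is posted publicly, it should be a dated, justified amendment made by the blinded investigators before the code is broken. Fixing the choice then also avoids a dispute if the adjusted and unadjusted limits fall on opposite sides of the margin.
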